### Statistical analysis

SPSS 19.0 software will be used. For all statistical tests, *P* < 0.05 will be considered to be statistically significant. Continuous data will be presented as mean ± standard deviation (M±SD), while dichotomous data will be presented as a proportion. The independent sample *t* test or *χ*^2^ test will be used to compare demographic data and other baseline indicators to measure the equilibria between the two groups.

Covariance analysis will be used for continuous data and logistic regression analysis will be used for dichotomous data, which will be adjusted according to baseline and dosages of loxoprofen sodium. The results will be presented as mean difference or odds ratio, providing a 95% confidence interval (CI). Intention to treat analysis (ITT) will be carried out for all the randomized patients. The last observation carried forward (LOCF) method and the maximum likelihood regression will be used for the missing data of primary outcome.

The per-protocol (PP) set will include only those who complete at least three sessions and all planned follow-ups and have no major protocol violations (taking other drugs during the trial, etc.). The ITT set will be used for primary analysis, and the PP set will be used as in the sensitivity analysis.

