**Methods/design:**

This is a parallel-group, assessor-blinded randomized controlled trial. Two hundred patients with KOA will be recruited and randomly assigned to two groups (group A or group D) in a 1:1 ratio. Patients in group A will receive acupotomy and topical diclofenac diethylamine for 4 weeks, while patients in group D will receive topical diclofenac diethylamine alone for 4 weeks. The primary outcome will be the response rate—the proportion of patients who achieve the minimal clinically important improvement in pain and function at week 4 compared with baseline. Secondary outcomes will include pain, function, quality of life, the use of rescue medicine (loxoprofen sodium), and adverse events at weeks 4, 8, and 24 after randomization. Besides, joint fluid and serum will be collected to assess the level of inflammatory cytokines, like TNF-α, IL-1β, and MMP-3.

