### Blinding

The nature of acupotomy means that patients and acupotomy doctors cannot be blinded during the treatment. Outcome assessors and statisticians will be blinded to group assignments. In this study, acupotomy doctor, outcome assessors, and statisticians will be independent.

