### Interventions

Patients in both groups will be prescribed diclofenac diethylamine emulgel (Voltalin, 1 g emulgel contains the main ingredient dichlorophenic acid diethylamine 10 mg, Beijing Novartis Pharma Ltd) of 3–4 times per day. A proper amount of diclofenac diethylamine emulgel will be applied according to the size of the knee pain area, then a gentle rub will be needed to make it penetrate the skin. The course of treatment will be 4 weeks. And each patient will be given a diary to keep track of how many times they used Voltalin each day. During the study period, loxoprofen sodium tablets (Loxonin, Dachi Sankyo Pharma Ltd) will be provided as rescue medication in case of intolerable knee pain, with the usage documented by the outcome assessors. Besides, all other interventions, such as acupuncture, moxibustion, physical therapy, surgical procedures, and intra-articular injections for KOA, will be forbidden. Other medications that do not influence pain will be allowed.

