### Primary outcome measurement

The primary outcome will be the response rate. The response rate is the percentage of patients with improvement in average pain NRS of at least 2 points [24], which is regarded as a minimum clinically important difference, and in the Western Ontario and McMaster Universities Osteoarthritis Index (WOMAC) [25] function subscale score of at least 6 points [24] at week 4 compared with baseline. The NRS is a digital scale using “0” to “10” to indicate the severity of the average pain over the last week, with “0” representing painless and “10” representing the most severe pain. The WOMAC function subscale (Likert version 3.1) consists of 17 questions (each scored from 0 to 4) relating to the difficulty experienced due to knee osteoarthritis, with higher scores referring to poorer knee function.

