### Secondary outcome measurements

The NRS and WOMAC pain subscale will be used to measure the average pain over the last week at weeks 0, 4, 8, and 24. WOMAC pain subscale ranges from 0 to 20. It has five items assessing the severity of pain in five different conditions, with higher scores indicating worse pain.

The WOMAC function subscale will be used to measure the physical function at weeks 0, 4, 8, and 24. The WOMAC function subscale ranges from 0 to 68 and includes 17 items, with lower scores indicating better function.

The WOMAC stiffness subscale will be used to measure the degree of stiffness of the knee at weeks 0, 4, 8, and 24. The WOMAC stiffness subscale ranges from 0 to 8 and includes two items, with higher scores indicating more stiffness.

The 12-item Short-Form Health Survey (SF-12) [26] will be used to assess the quality of life at weeks 0, 4, 8, and 20. SF-12 includes the mental and physical domains. Each domain ranges from 0 to 100, with higher scores indicating a better quality of life.

The use of rescue medicine (loxoprofen sodium tablets) will also be recorded throughout the trial.

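### The outcome models adjust for loxoprofen dose, a post-randomisation variable and secondary outcome, so the primary comparison can be biased and lose power

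*Protocol article*

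**What the plan says.** The Statistical analysis section of the protocol article names the models: "Covariance analysis will be used for continuous data and logistic regression analysis will be used for dichotomous data". The rest of that sentence fixes the covariates for them: "which will be adjusted according to baseline and dosages of loxoprofen sodium". The section gives no model without the loxoprofen term and no reason for including it. It also says that "The ITT set will be used for primary analysis".

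Under Interventions, loxoprofen tablets "will be provided as rescue medication in case of intolerable knee pain, with the usage documented by the outcome assessors". The abstract's methods paragraph names rescue use among the secondary outcomes: "Secondary outcomes will include pain, function, quality of life, the use of rescue medicine (loxoprofen sodium), and adverse events". The section on secondary outcome measurements repeats this: "The use of rescue medicine (loxoprofen sodium tablets) will also be recorded throughout the trial".

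The primary outcome is binary ("The primary outcome will be the response rate"). Response requires improvement of at least 2 points in pain NRS and at least 6 points in WOMAC function at week 4. It is therefore analysed by the logistic model that carries the loxoprofen term.

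**The concern.** Loxoprofen dose is not a baseline characteristic. It accrues during the trial and is triggered by the symptom that the NRS half of the primary outcome measures. Conditioning on it causes two problems.

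- **Mediation.** If acupotomy relieves pain, it should also reduce rescue use. Comparing patients at equal rescue dose then removes part of the effect that the trial sets out to measure.
- **Collider bias.** Underlying severity drives both rescue use and response. If the arms differ in rescue use for any reason, patients with the same dose in the two arms are no longer comparable in severity. Such differences are plausible here. The Blinding section says "The nature of acupotomy means that patients and acupotomy doctors cannot be blinded during the treatment", and only the acupotomy arm has weekly hospital treatment visits.

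In either case the adjusted odds ratio or mean difference is not the total effect of adding acupotomy, and randomisation no longer protects the comparison. Estimate, power and type I error of the primary analysis are all exposed.

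**Working it through.** **1. Inputs from the document.** Response 60% (control) and 80% (acupotomy), two-sided 5%, power 80%, 1:1 allocation, 80 per group, 20% dropout, 100 per group (Sample size section). Covariates are baseline and loxoprofen dose (Statistical analysis section). No rescue rate or dose by arm is given.

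**2. The plan's own figure.** With mean proportion 0.7:

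- Pooled: n = [1.96·√(2·0.7·0.3) + 0.842·√(0.6·0.4 + 0.8·0.2)]² / 0.2² = 81.2, so 82.
- Unpooled: n = (0.24 + 0.16)·(1.96 + 0.842)² / 0.2² = 78.5, so 79.
- Dropout: 80 / (1 − 0.2) = 100.

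The stated 80 and 100 reproduce within rounding. Power at 80 per group is 0.794 (pooled) or 0.807 (unpooled). The odds ratio is (0.8/0.2)/(0.6/0.4) = 2.67. The trial is thus sized for a contrast that is not conditional on rescue dose.

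**3. How far the adjusted effect moves (illustrative, 400,000 simulated patients).** Let A be the arm, U standard normal severity, and e₁, e₂, e₃ independent standard normal errors.

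- On-treatment pain P = U − t·A + 0.7·e₁
- Rescue dose R = max(0, b·P + 0.7·e₂)
- Final pain F = P − g·R + 0.7·e₃; response if F is below the control arm's 60th percentile

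The effect t is set so that about 80% respond in the acupotomy arm. Here b is how strongly pain drives dose and g is the pain relief per unit of dose.

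| b | g | OR without dose | OR with dose | Standardised risk difference, with dose |
|---|---|---|---|---|
| 0 | 0 | 2.70 | 2.70 | 0.20 |
| 0.3 | 0 / 0.3 | 2.60 / 2.64 | 2.38 / 2.44 | 0.165 / 0.175 |
| 0.6 | 0 / 0.3 | 2.70 / 2.69 | 2.11 / 2.14 | 0.12 / 0.14 |
| 1.0 | 0 / 0.3 | 2.68 / 2.62 | 1.80 / 1.85 | 0.08 / 0.10 |

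The true risk difference is 0.20 throughout. Three further runs set t = 0 and b = 0.6, so treatment has no effect on response:

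- No effect on rescue either (g = 0.3): adjusted OR 1.00.
- Treatment lowers the rescue term by 0.5 (g = 0): adjusted OR 0.64.
- Treatment raises the rescue term by 0.5 (g = 0): adjusted OR 1.75.

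**4. Power and type I error (illustrative, 80 per arm, 3,000 simulated trials).** A latent-normal model was used in which about half the patients take no tablets and rescue use is correlated with lack of improvement. Logistic regression was fitted with and without dose. The false-positive columns assume no effect on response but rescue use shifted between arms. Each range spans the two directions of shift.

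| Correlation | Power without dose | Power with dose | Median OR with dose | False positives, 0.5 SD shift | False positives, 0.8 SD shift |
|---|---|---|---|---|---|
| 0.3 | about 0.79–0.80 | 0.76 | 2.7 | 8–9% | 10–15% |
| 0.5 | about 0.79–0.80 | 0.68 | 2.5 | 13–19% | 22–40% |
| 0.7 | about 0.79–0.80 | 0.50 | 2.3 | 27–41% | 48–79% |

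The median OR without dose is about 2.7. With no effect on response or rescue, rejection is about 5%. Repeat runs of similar models gave powers of 0.76–0.77, 0.66–0.67 and 0.50.

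Direction, from a 1,000-trial run of a similar model at correlations 0.3, 0.5 and 0.7 with a 0.5 SD shift: less rescue in the acupotomy arm gives spurious ORs of 0.86, 0.72 and 0.58; more rescue gives 1.23, 1.52 and 2.07.

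The simulations contain no baseline covariates. Baseline adjustment would absorb part of the severity path, but not the dependence of dose on pain during treatment.

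**The case against.** The best defence is that rescue analgesia muddies a pain comparison: if one arm takes more tablets, the analyst should allow for it. That would be a different question, namely the effect had no rescue been taken. It needs assumptions that the plan does not state, and entering dose as a regressor does not answer it when pain drives both dose and outcome.

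Several narrower objections have force.

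- Bias is not automatic. If treatment leaves rescue use unchanged, directly and through pain, the adjusted test keeps its level.
- The size cannot be derived from the document. The two sets of simulations differ in their odds ratios (2.4 to 1.8 against 2.7 to 2.3), and at correlation 0.3 the second shows no shrinkage.
- Odds ratios with and without a covariate differ partly through non-collapsibility. The fall in the standardised risk difference and the loss of power are cleaner evidence.
- If acupotomy lowers rescue use, the expected bias is against acupotomy. A false claim of benefit requires more rescue use in that arm.
- Read literally, the blanket wording would adjust rescue use for itself. No analyst would do that, so this shows loose drafting and adds no harm.
- The sentence could be read as attaching the adjustment to the logistic model only. That reading still covers the primary outcome.

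These points limit how the size should be reported. None of them justifies the covariate. Nor is this a detail left to a fuller document: the article states the adjustment outright.

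**Conclusion.** The concern stands and should be fixed before analysis. The plan makes a rescue-conditional estimate its primary result while calling the analysis ITT, and it sizes the trial on a contrast without that condition.

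Under the planned 60% versus 80%, and assuming that dose follows pain, power falls from about 80% to between 76% and 50% over correlations of 0.3 to 0.7. If rescue use differs between arms without any effect on response, the false-positive rate rises to 8–41% for a 0.5 SD shift over the same correlations. The direction depends on which arm takes more rescue. These figures are illustrative. That the adjusted coefficient is not the effect of assignment whenever treatment alters rescue use follows from the design and does not depend on them.

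**What to change.** Remove loxoprofen dose from the adjustment set in the Statistical analysis section. Replacement text could read: *The week-4 response will be analysed by logistic regression on treatment group, baseline NRS and baseline WOMAC function. Each continuous outcome will be analysed by ANCOVA on treatment group and its own baseline value. Loxoprofen use will not be a covariate; it will be compared between groups as a secondary outcome.* The two named baseline covariates are one reasonable reading of the plan's reference to baseline.

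If the sponsor wants rescue use reflected in the primary result, it can pre-specify a sensitivity analysis that counts patients who used rescue during the week-4 NRS recall period as non-responders. That needs dated rescue intake. The article describes a daily patient diary for the gel only and does not say whether rescue intake is dated, so this should be checked first.

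The core change costs one sentence. It needs no new data, and the sample size of 100 per group stands.

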### Sample size

The primary outcome in this study is the response rate, and the allocation ratio between the two groups is 1:1. A bilateral difference test will be used to calculate the sample size. According to a previous review, the response rate of the diclofenac diethylamine emulgel for KOA is assumed to be 60% [28]. The response rate in the acupotomy group is assumed to be 80% based on preliminary clinical experience. The sample size of each group is 80 calculated by PASS 11.0.7 (NCSS, LLC, USA) software with a two-sided significance level of 5% and power of 80%. Considering a 20% drop-out rate, the final sample size of each group will be 100, with a total of 200.

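### For the week-4 primary outcome LOCF amounts to scoring every missing patient as a non-responder, is not ranked against the second named method, and does not match the sample-size calculation

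*Protocol article*

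**What the plan says.** Under Primary outcome measurement, a responder must improve by at least 2 points on the average pain NRS and must also improve in the WOMAC "function subscale score of at least 6 points [24] at week 4 compared with baseline".

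Under Secondary outcome measurements, the visits for the two components are listed: "The NRS and WOMAC pain subscale will be used to measure the average pain over the last week at weeks 0, 4, 8, and 24", and "The WOMAC function subscale will be used to measure the physical function at weeks 0, 4, 8, and 24". Nothing is listed between weeks 0 and 4.

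Under Statistical analysis, the rule for missing data is: "The last observation carried forward (LOCF) method and the maximum likelihood regression will be used for the missing data of primary outcome". The same section states "Intention to treat analysis (ITT) will be carried out for all the randomized patients" and gives one hierarchy: "The ITT set will be used for primary analysis, and the PP set will be used as in the sensitivity analysis". That ranks analysis sets, not missing-data methods.

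Under Sample size, the assumptions are response of 60% with gel alone and 80% with acupotomy, two-sided 5% significance and 80% power. This gives 80 per group, raised to 100 for 20% drop-out.

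**The concern.** LOCF needs an intermediate post-baseline value to carry. Here there is none before week 4, so it becomes baseline carried forward. A missing patient has zero change on both components and fails the response definition automatically. A patient who misses week 4 but attends week 8 is still scored this way, because LOCF does not look back from later visits.

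Three things follow.

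- The plan uses a non-responder rule without saying so.
- That rule and a likelihood method estimate different quantities. Joining them without an order leaves the primary result undefined and the choice open until results exist.
- The sample size was set for an analysis in which drop-outs are absent, not one in which they are counted as failures. The stated power does not apply to the LOCF analysis.

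**Working it through.** **Inputs.** Response 80% (A) and 60% (D), two-sided 5%, 80% power, 80 per group, 20% drop-out and 100 per group are from Sample size. Visit weeks are from Secondary outcome measurements. The drop-out split by arm and the amount missing at week 4 are not given, so the values below are assumptions. All power figures are for an unadjusted pooled two-sided z test by exact enumeration, unless stated. The planned logistic model adjusts for baseline and loxoprofen dose, which does not alter the mechanism.

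**1. The plan's own figure.** The unpooled formula is n = (1.96 + 0.842)² × (0.8×0.2 + 0.6×0.4) / 0.2² = 78.5, so 79 per group. The arcsine formula gives 80.3 and the pooled formula 82. At 80 per group power is 80.1%. Inflation: 80 / (1 − 0.20) = 100. The stated figures reproduce, on the footing that 80 patients per group remain for analysis.

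**2. What LOCF does at week 4.** The carried value is baseline, so change is 0, which is below both 2 and 6 points: non-responder. With drop-out d unrelated to response p within an arm, the expected LOCF response is p × (1 − d), with all 100 patients in the denominator.

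**3. Equal drop-out, true 80% versus 60%, 100 per arm.**

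| Missing per arm | LOCF response, A vs D | Difference | Power |
|---|---|---|---|
| 5% | 0.80×0.95 = 76% vs 0.60×0.95 = 57% | 19 points | 82% |
| 10% | 0.80×0.90 = 72% vs 0.60×0.90 = 54% | 18 points | 76% |
| 20% | 0.80×0.80 = 64% vs 0.60×0.80 = 48% | 16 points | 64% |

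A likelihood analysis under missing at random targets 80% − 60% = 20 points in every row. At 20% missing it has about 80% power on 80 observed per arm, as planned. On the odds-ratio scale, which is how the result will be reported, the contrast at 20% missing is (0.64/0.36)/(0.48/0.52) = 1.93 for LOCF against (0.80/0.20)/(0.60/0.40) = 2.67.

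**4. Unequal drop-out, no true effect (60% in both arms).** This assumes that drop-outs would have responded like completers.

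| Missing, A vs D | LOCF response, A vs D | Rejection rate |
|---|---|---|
| 20% vs 20% | 48% vs 48% | 5.6% |
| 5% vs 10% | 57% vs 54% | 7.7% |
| 10% vs 20% | 54% vs 48% | 14.7% |

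Swapping the arms gives the same rejection rates with the spurious difference favouring D. With a real benefit, more loss in A would mask it: 25% in A and 15% in D gives 0.80×0.75 = 60% vs 0.60×0.85 = 51%, or 9 points instead of 20.

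**The case against.** The strongest reply is that non-responder imputation is a recognised rule for responder endpoints. Patients unwilling to return may well be those who did not improve. If so, counting them as failures is close to right and the missing-at-random estimate is the biased one. This stands as far as it goes: the rule can be defended if it is declared as the target and powered for. Here it appears only as a by-product of LOCF, beside a second method that assumes something else.

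One could also argue that 60% and 80% already count drop-outs as failures. Then 100 per group would give about 88% power (normal approximation). The document does not say this, and the inflation from 80 to 100 would then have no purpose.

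The 20% drop-out has no time point in a trial followed to week 24, so loss by week 4 may be lower. That is fair, and is why the 5% and 10% rows are shown. Blinded, independent statisticians limit selective choice between the methods but do not rank them.

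A reader might infer several stronger points that the document does not support:

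- **Unequal drop-out is likely.** Lack of blinding makes it plausible. Treatment is free in both arms and group A has weekly invasive visits, so even the direction is unclear.
- **Very large error rates.** These need about 30% missing in one arm at week 4, above the plan's own 20% limit.
- **The likelihood method is merely complete-case logistic regression.** The method is not defined, and it could use weeks 8 and 24.
- **Secondary outcomes will be analysed with missing patients dropped.** The article is silent on this, and such detail may sit in a document not shown.

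**Conclusion.** The point holds. On the listed visit weeks (the schedule figure is not available), week-4 LOCF is baseline carried forward and equals non-response. It is paired with a method that targets a different quantity, and nothing in the plan says which gives the primary result. This is stated in the article itself, so it is not a detail left to an analysis plan.

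The firmest consequence needs no assumption of unequal drop-out. At the planned rates, with drop-out unrelated to response, the LOCF effect is 16 points with power of about 64% if 20% are missing at week 4, and 18 points with about 76% if 10% are missing. Only at about 5% missing does power stay above 80%. The effect of unequal drop-out is illustrative: rejection under no effect of about 8% (5% vs 10% missing) to 15% (10% vs 20%), conditional on drop-outs responding like completers. The bias can run either way, so LOCF cannot be relied on as conservative.

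**What to change.** Before unblinding, name one primary missing-data method for the week-4 responder endpoint. A suitable choice is multiple imputation by arm of week-4 NRS and WOMAC function, using baseline scores, the week-8 and week-24 visits and rescue use, with response derived after imputation. Drop LOCF as a primary method. Label non-responder imputation as a sensitivity analysis under that name, and add a tipping-point analysis.

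If the investigators prefer non-responder imputation as primary, they should state it as such and redo the power calculation with drop-outs counted as failures. At 64% versus 48%, the pooled formula needs 150 per arm for 80% power.

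The recommended change costs wording and modest programming, and no new data. Its downside is reliance on missing at random, which the tipping-point analysis probes.

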The patients in the acupotomy group will receive acupotomy in the hospital one time per week for 4 weeks. A sterilized, disposable needle-scalpel (Hanzhang No.4, length: 60 mm, diameter: 0.6 mm, Beijing Hanzhang Medical Device Co., Ltd) will be used. To keep the consistency and standardization of the operation, the acupotomy will be performed by an experienced doctor who has a Chinese medicine practitioner license and has been qualified for at least 15 years according to the basic operating procedures of acupotomy in the *Principles of Acupotomy*. The appropriate body position will be chosen depending on the location of the operation, such as supine, prone or side-lying position. The medial collateral ligaments, lateral collateral ligaments, hamstring muscle, quadriceps femoris, iliotibial band, popliteus muscle, anserine bursa, subpatellar fat pad, and the peripatellar area will be touched and pressed, then the spots with induration and cordlike tissue will be identified as positive points. Generally, 5–7 positive points will be selected in light of the specific pain sites, functional limitations, and imaging examination results of the patients’ joints. The selected points will be marked with gentian violet, and then the surrounding skin will be disinfected with iodophor. After sterile skin preparation, a needle-scalpel will penetrate the skin and gradually go deeper. When feeling a sense of toughness or resistance under the needle-scalpel, the manipulation of acupotomy is performed. After treatment completion, the doctor will check for any abnormality and bleeding, then apply the Band-Aid to the pinhole.

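### The per-protocol set for the week-4 primary outcome tests treatment adherence in group A only and makes membership depend on visits after week 4

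*Protocol article*

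**What the plan says.** The Statistical analysis section of the protocol article defines the per-protocol (PP) set in one sentence: "The per-protocol (PP) set will include only those who complete at least three sessions and all planned follow-ups", and who "have no major protocol violations (taking other drugs during the trial, etc".). It names no arm. The next sentence gives the set its role: "The ITT set will be used for primary analysis, and the PP set will be used as in the sensitivity analysis".

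Four other places bear on how that definition works:

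- **Sessions.** Interventions: "The patients in the acupotomy group will receive acupotomy in the hospital one time per week for 4 weeks". The abstract says of the other arm that "patients in group D will receive topical diclofenac diethylamine alone for 4 weeks".
- **Gel use.** Interventions: "each patient will be given a diary to keep track of how many times they used Voltalin each day". This covers both groups.
- **Primary outcome.** Primary outcome measurement sets response as an improvement of at least 2 points on the pain NRS together with an improvement in the WOMAC "function subscale score of at least 6 points [24] at week 4 compared with baseline".
- **Follow-up.** The abstract and Secondary outcome measurements place visits at weeks 4, 8 and 24. The SF-12 is listed at week 20 in the latter section, so the full set of planned visits is itself not quite clear.

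**The concern.** A PP analysis is read as a check on the intention-to-treat (ITT) result. It serves that purpose only if the same kind of patient is kept in each arm and if membership is settled by what happened up to the time of the outcome. The stated definition is weak on both counts.

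First, a session count can be met or failed only in group A. Under Blinding, patients know their treatment, and the Drop-out criteria include unwillingness to return for treatment and serious adverse events. Patients who stop acupotomy early may therefore differ in response from those who continue. Patients in group D who stop using the gel face no named test.

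Second, requiring every follow-up visit makes membership for a week-4 outcome depend on attendance up to 20 weeks later (24 - 4 = 20). That attendance may depend on whether the patient responded, and the rule discards complete primary outcome data.

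At stake is the reading of the only analysis that the article labels a sensitivity analysis. If the filter favours group A, agreement between PP and ITT would reassure more than it should.

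**Working it through.** **Planning figures.** The Sample size section assumes 60% response on gel and 80% with acupotomy, two-sided 5% significance and 80% power, and states 80 per group. The usual two-proportion formula gives 82 per group with pooled variance and 79 with unpooled variance, so 80 is reproduced within tolerance. With 20% drop-out, 80/(1 - 0.20) = 100 per group, as stated. The 60% rate and the 20% loss are used below. All stopping and retention rates are assumptions, because the article gives none.

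**Session rule applied to group A only, no true effect.** Let f be the share of group A that stops early and r the response rate among those who stop. Response among those kept is (0.60 - f·r)/(1 - f). With group D left at 60%, the false difference is

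(0.60 - f·r)/(1 - f) - 0.60 = f·(0.60 - r)/(1 - f).

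| f | r | Group A in PP set | False difference |
|---|---|---|---|
| 0.10 | 0.40 | 0.56/0.90 = 62.2% | +2.2 points |
| 0.15 | 0.30 | 0.555/0.85 = 65.3% | +5.3 points |
| 0.20 | 0.20 | 0.56/0.80 = 70.0% | +10.0 points |

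The formula also shows the other cases. If r = 0.60, so that stopping is unrelated to response, the difference is 0. If r is above 0.60, so that early improvers stop, it is negative and works against acupotomy.

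**Some selection in group D as well.** If group A loses 15% with 30% response and group D loses 10% with 40% response, the PP rates are 65.3% and 62.2%. The false difference is 3.1 points instead of 5.3.

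**A second parameterisation.** Let kR and kN be the shares of responders and non-responders kept. The PP response rate is p·kR/(p·kR + (1 - p)·kN). With p = 0.60, kR = 0.90 and selection in group A only:

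- kN = 0.80: 0.54/(0.54 + 0.32) = 62.8%, or +2.8 points.
- kN = 0.65: 0.54/(0.54 + 0.26) = 67.5%, or +7.5 points. Group A retention is 0.54 + 0.26 = 80%, which matches the planned 20% loss.
- kN = 0.50: 0.54/(0.54 + 0.20) = 73.0%, or +13.0 points.

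**Follow-up rule, which applies to both arms.** Take kR = 0.90 and kN = 0.65 in each arm. With no true effect both arms show 67.5% and the difference is 0. With the planned 80% against 60%, group A shows 0.72/(0.72 + 0.13) = 84.7% and group D 67.5%, a difference of 17.2 points instead of 20. So this rule can also shrink a real effect, and its direction cannot be assumed.

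**The case against.** **Group D would be empty.** A reader might infer this, since no arm is named and group D has no sessions. The documents do not support it as the intended meaning. The abstract and Interventions make plain that sessions belong to group A, and an analyst would apply the rule there only. The asymmetry remains under that reading.

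**The drug criterion contradicts Interventions.** A reader might infer this too, because Interventions supplies rescue loxoprofen and says "Other medications that do not influence pain will be allowed". But other drugs are cited only as an example of a major protocol violation, and a permitted drug is most naturally not a violation. The wording is loose and would gain from a cross-reference. It is not a contradiction.

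**Gel non-use may already count as a violation.** The list of violations is open-ended, and an article need not print all of it. That is fair, and the absence of a full list is no finding. What stands is that the article does state an adherence rule, and the rule it states can operate in one arm only.

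**One PP set may be meant to serve every time point.** That would explain the follow-up rule, which treats both arms alike. It does not make the rule suitable for the week-4 outcome.

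**The consequence is limited.** ITT on all randomized patients is primary, three of four sessions is a lenient threshold, and some selection is inherent in any PP analysis. The section also names last observation carried forward and maximum likelihood regression for missing primary data, although it does not call either a sensitivity analysis. All of this stands and keeps the point modest.

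**Conclusion.** The PP definition is badly fixed for the week-4 primary outcome in two respects: adherence is tested by name in group A only, and membership depends on attendance after the outcome has been measured. Both follow from the text without any assumption.

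The size and direction of any bias are not known. The 2 to 10 points in favour of acupotomy rest on assumed stopping of 10-20% in group A, 20-40% response among those who stop, no true effect and no filtering of group D. Other plausible inputs give less, zero or the reverse. It would be wrong to conclude that the PP result must favour acupotomy, and the primary ITT estimate does not change. The definition should still be corrected, because PP is the check the article offers on its primary result and the remedy is wording.

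**What to change.** Amend the PP definition before group codes are released to the statistician:

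1. For the week-4 outcome, require only the baseline and week-4 pain NRS and WOMAC function assessments. Where a PP analysis of a later outcome is wanted, require the visit for that outcome.
2. State that the three-session rule applies to group A.
3. Add a gel-diary adherence criterion common to both arms, with its threshold fixed in advance.
4. Define medication violations by pointing to what the Interventions section forbids and allows. This is a clarification only.

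The cost is small. The diary is already collected, so no new data are needed. The downsides are slightly more analysis work and PP sets that differ by time point. Group A will still carry one filter that group D does not, so the PP result should be read with that in mind.
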